**Figure 2. Study design**

Communes randomly assigned

Twice weekly multiple micronutrients

Daily iron intervention

Twice weekly iron intervention

Eligible pregnant women <16 weeks, consent, interview, ht, wt, arm circ, Hb, micronutrient tests*. Twice weekly iron commenced.

Six weekly monitoring

Eligible pregnant women <16 weeks, consent, interview, ht, wt, arm circ, Hb, micronutrient tests*. Twice weekly MMN commenced.

Six weekly monitoring

Eligible pregnant women <16 weeks, consent, interview, ht, wt, arm circ, Hb, micronutrient tests* Daily iron commenced.

Six weekly monitoring

32 weeks gestation: interview, anthropometry, Hb, micronutrient tests.

32 weeks: interview, anthropometry, Hb, micronutrient tests.

32 weeks: interview, anthropometry, Hb, micronutrient tests.

Birth weight, length, HC and outcomes

Birth weight, length, HC and outcomes

Birth weight, length, HC and outcomes

6 months Postpartum-interview, maternal anthropometry, Hb, ferritin; infant ht, wt, HC, Hb, ferritin, developmental screening

6 months Postpartum-interview, maternal anthropometry, Hb, ferritin; infant ht, wt, HC, Hb, ferritin, developmental screening

6 months Postpartum-interview, maternal anthropometry, Hb, ferritin; infant ht, wt, HC, Hb, ferritin, developmental screening

* Micronutrients to be tested include ferritin, TfR, folate, vitamin B12.
Hb = haemoglobin, Ht = height, Wt = weight, TfR = transferrin receptor, MMN = multiple micronutrients, HC = head circumference.

Measures: Data will be collected via blood tests and a range of measures including structured individual interviews using psychometric instruments, maternal and infant anthropometry, compliance and side-effects, birth records and assessment of infant growth and developmental screening as described below.

Aim 1. To compare the effect of twice weekly provision of IFA or MMN supplements, with the recommended daily provision of IFA supplements during pregnancy on maternal and infant outcomes during pregnancy and the first 6 months of life (including the primary outcome of birth weight; and secondary outcomes of maternal haemoglobin and ferritin at 32 weeks, and infant height for age z scores, haemoglobin, ferritin and cognitive developmental scores at 6 months of age).

*Rationale: Iron deficiency in pregnancy is associated with increased maternal mortality, preterm delivery, low birth weight* [4] *and low iron stores in infancy* [16]*. Low birth weight infants have higher mortality rates, and are more likely to be stunted. Stunting is a good indicator of later poor performance at school* [44]*. Iron deficiency in infancy may also contribute to poor cognitive development and later school performance* [4],[45]*.* *Iron deficiency anaemia is widely prevalent in pregnant women despite global and national policies for daily provision of iron supplementation in most countries. This is thought to be because of poor availability of supplements at the primary level, and poor compliance because of unpleasant side-effects. On the other hand, weekly iron supplementation has been shown to be effective in improving iron status in non-pregnant women in Vietnam and elsewhere, and in small studies in pregnant women. This approach has the advantage of few side-effects and easier distribution. Furthermore, emerging evidence suggests that small daily doses or iron during pregnancy, as well as weekly dosing starting early in pregnancy, are safer and essentially as efficacious as daily iron in preventing iron deficiency and improving iron stores* [20]*. Daily provision of MMN supplementation may also have advantages over daily IFA- as Zheng et al recently showed increased birth weight with their use in pregnant women in China* [3]*. It remains to be determined if weekly provision of IFA or MMN will be superior to daily provision of IFA, when given in a large cluster-randomized controlled trial in a developing setting, using infant birthweight as the primary outcome.*

Maternal socio-demographic factors – will be measured in one-to one interviews using previously developed and pilot-tested questions. These interviews will occur after obtaining signed informed consent, and will be conducted by experienced RTCCD staff that have had refresher training as mentioned above. For women receiving a twice weekly supplement the researchers will be blinded to the intervention.

Maternal anaemia and micronutrient deficiencies: In women who agree, venipuncture blood samples will be collected at enrolment, 32 weeks gestation and 6 months postpartum by staff trained in the procedure. Hb will be measured in the field using HemoCue, and serum samples frozen and transported to Hanoi for testing at the National Institute of Nutrition (or accredited laboratory in Australia or US – depending on cost) for iron indices and other micronutrient indicators (serum ferritin61, transferrin receptor, folate, vitamin B12) using standard laboratory methodology. Laboratory staff will be not be aware of the intervention being taken by a participant or any other study data.

Maternal and Infant anthropometry Maternal anthropometry will be assessed by mid-upper arm circumference, body weight and height in all participants at enrolment, 32 weeks gestation, and, six months postpartum This provides a portable, universally applicable, inexpensive and non-invasive technique for assessing body composition and reflects both health and nutritional status [46]. Mid-upper arm circumference will be measured at the midpoint between the acromion and the olecranon process. The arm circumference will be recorded to the nearest 0.1cm. Mother's height will be measured with a portable stadiometer (Seca 214, Hamburg, Germany) and weight with a mother-infant scale (Seca 872, Hamburg, Germany).

All commune health centers involved in the study will be provided with new tabletop digital infant weighing scales that measure to 10 grams (supplied by BF20510, LAICA, Italy) as existing scales do not have the required sensitivity. In the event of a home birth, commune health workers will be advised to measure and weigh the baby as soon as possible after birth (at least within 3 days), either at the commune health station or in the home.

Measurements of child length (crown-heel) will be made using a portable infantometer (Seca 210, Hamburg, Germany), mother's height with a portable stadiometer (Seca 214, Hamburg, Germany), child's weight with a mother-infant scale (Seca 872, Hamburg, Germany). Growth (height-for-age, weight-for-age, and weight-for-length) will be evaluated using the World Health Organization Child Growth Standards 2006[47]. Head circumference will be measured with a non-stretchable tape, using standard procedures.

Standardization of anthropometric measurements: Trained members of the research team will make the maternal and infant anthropometric measurements. A nominated commune health worker and birth attendant will measure birthweights in each commune in the study. These staff will be trained using WHO and CDC resources[48-50].Nominated labor ward staff in the five district hospitals will be included in these training sessions. Each measurement will be made in triplicate bytwoobservers and the middle value used. In addition the monitors and field supervisors will provide ongoing support for commune staff and ensure that scales and measurements are standardized across all sites.

Compliance and side-effects – each participant will be visited by a member of the research team every six weeks, who will collect old blister packs and record the number of supplements that have been removed from the pack. They will ask about compliance, side-effects and any other health issues, as well as providing new supplements.

Infant anaemia and iron deficiency

If mothers agree, venipuncture blood samples will be collected from infants at 6 months of age and Hb and iron stores (ferritin) will be measured as above.

Infant development screening Advice from researchers with experience in this area ([name] – Mexico) and a review of the literature suggests that a comprehensive assessment using the Bayley Scales of Infant Development III (BSID) is the best approach in this situation [51]. This will provide an infant development score that can be compared between the study groups, and the assessment will take 30-45 minutes. The BSID has language, cognitive, social-emotional, motor and adaptive behavior (caregiver report) subscales that can be scored separately, so that domain-specific assessments can be made, providing comprehensive developmental screening. We plan to recruit local psychologists and paediatricians with experience in developmental screening and provide them with training in the use of the BSID using either local or international experts. The instrument will be pilot tested in Hanam province and adapted to the local cultural context. The infant assessment team will be additional to the core research team and will not have access to other maternal or infant data, including iron status or maternal depression scores, thereby limiting bias.

Aim 2. To compare the effect of twice-weekly provision of IFA supplements with twice-weekly MMN during pregnancy on maternal and infant outcomes during pregnancy and the first six months of life, using similar outcomes to Aim 1.

*Rationale:* *Daily MMN in pregnancy have been shown in some studies to have advantages over daily IFA, especially in terms of birth weight* [3,32]*. Similarly, twice-weekly MMN may be slightly more efficacious than twice-weekly IFA as micronutrients such as vitamin C may increase iron absorption, and folic acid, vitamin B12 and vitamin A may improve Hb levels. However, the presence of zinc in the MMN supplements may lead to a reduction in iron absorption* [52]. *It remains to be determined* if there are any significant differences in clinical outcomes between the twice weekly provision of IFA and MMN.

We will compare outcomes in the twice weekly IFA and MMN arms of the trial. However, we expect any differences in outcomes to be small given that both formulations contain 60mg elemental iron. We will use similar analysis techniques for Aim 1. Estimates (95% confidence intervals) of the difference in mean haemoglobin levels at 32 weeks, ferritin levels at 32 weeks, birthweight and height for age (at 6 months of age) between the two weekly trial arms will be derived using linear mixed-effects modeling incorporating a random effect for commune to allow for clustering. For the outcomes haemoglobin and ferritin, the statistical analysis will adjust for the baseline measurement.

**Table 1: Schedule of administration of maternal and infant assessments**

**1. Mothers**

| **Measure** | **Enrolment <16 wks gestation** | **32 weeks gestation** | **6 months postpartum** |
| --- | --- | --- | --- |
| HemaCue test for Hb | √ | √ | √ |
| Venipuncture blood sample | √ | √ | √ |
| Maternal anthropometry (ht, wt, Mid upper arm circumference) | √ | √ | √ |
| Study-specific interview | √ | √ | √ |

**2. Infants**

| **Measure** | **Birth** | **6 months of age** |
| --- | --- | --- |
| Birth assessment | √ |  |
| Infant anthropometry (wt, length, HC) | √ | √ |
| Developmental Screening using Bayley Scales |  | √ |
| HemaCue test for Hb |  | √ |
| Venipuncture blood sample |  | √ |

Sample size calculations

Hb data from pregnant women in Hanam province on which to base our sample size estimates and data regarding the number of pregnant women available for recruitment has recently been collected in an observational study. There were on average 10 eligible pregnant women of 12 to 20 weeks gestation per commune (mean 10, range 2-20). In the proposed study all eligible pregnant women in communes allocated to each arm of this study will be invited to receive the intervention.

This cluster randomized trial will recruit 34 communes / 408 pregnant women per treatment arm (i.e. a total of 1224 women from 102 communes) where the average commune size is 12 women per commune and it is expected that 5% of women will be excluded due to pregnancy complications and 15% will be lost to follow-up.

With 95% confidence the above sample size has at least 80% statistical power to detect clinically important differences of 6 g/L for haemoglobin (power = 98%, SD=12g/L, ICC=0.12)[[1]](#footnote-2), 100g for birthweight (power = 81%, SD= 389g, ICC=0.03)[[2]](#footnote-3), and 0.3 for the height for age Z-score (power = 93%, SD=0.9, ICC=0.05)[[3]](#footnote-4). The above sample size calculations were performed using ‘sampsi’ and ‘sampclus’ in the statistical program Stata (StataCorp, College Station, TX, USA).

Our primary hypotheses (and sample size estimates) are based on continuous measurements to ensure that all information is included. The optimal Hb in late pregnancy is not clear as there is evidence that moderately low and higher haematocrits may impair birth outcomes. We are also interested in the absolute mean change of ferritin at 32 weeks, as this will reflect the effectiveness of the intervention in maintaining womens’ iron stores into the third trimester of pregnancy. This approach may reduce our power to asses change in percentage of women with anaemia or iron deficiency.

Data Management

Data will be recorded on paper forms and entered into a customized database by a trained data entry officer in the provincial office. It will be checked and cleaned by an epidemiologist in the Hanoi RTCCD office. The database will be developed in conjunction with Associate [name] (University of Sydney) and scientists at the National Institute for Nutrition who were involved in the Zeng et al. (2008) study in China. Stata (vs10) will be used for data analysis.

Statistical Analysis

[name] (Centre for Molecular, Environmental and Genetic Analytic Epidemiology, Melbourne School of Population Health, University of Melbourne) will oversee statistical analysis of trial data [58]. Estimates (95% confidence intervals) of the difference in mean haemoglobin levels at 32 weeks, ferritin levels at 32 weeks, birthweight and height for age (at 6 months of age) between the daily and weekly trial arms will be derived using linear mixed-effects modeling incorporating a random effect for commune to allow for clustering. For the outcomes haemoglobin and ferritin, the statistical analysis will adjust for the baseline measurement. Since the distribution of ferritin levels are typically skewed, these levels will be loge transformed before analysis and the comparison of levels between trial arms presented as the ratio of the geometric means.

All statistical analyses will be performed using the statistical program Stata, Version 10 (StataCorp, College Station, TX, USA).

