We have shown in a large population-based program that weekly iron-folic acid supplementation reduces anaemia rates in non-pregnant Vietnamese women by 52% over 12 months. A weekly regime of iron-folic acid or MMN supplementation started in adolescence and continued throughout the reproductive years, including in pregnancy, may result in better compliance by women, fewer side-effects and an easier administrative system, leading to increased availability of supplements to pregnant women. However, more information is needed about the use of intermittent supplementation in pregnancy with both iron-folic acid and MMN.

In this study, we will compare the effects of three different methods of iron supplementation in 1224 pregnant Vietnamese women on maternal haemoglobin and iron stores, infant birth weight, and infant anaemia, infant height, weight and developmental screening during the first 12 months of life. Maternal depression will be correlated with infant growth and development, after controlling for maternal iron status. Prior to the study we will consult widely with provincial health officials, community leaders, health workers and community members to ensure high levels of community participation in the project. All pregnant women who are <20 weeks gestation during the recruitment period will be invited to participate and will be assigned to one of three study arms depending on the commune they live in. Women will take either (i) two capsules of iron-folic acid per week (60 mg elemental iron/capsule), or (ii) one capsule of iron-folic acid per day (60mg iron/capsule), or (iii) two capsules of MMN per week (60mg iron/capsule). Women will have their height and weight measured at the third trimester, and at 6 months postpartum, as well as having blood tests to measure haemoglobin, iron stores and other micronutrients. Infant birth details will be recorded, and infant growth and development will be assessed at 6 months after birth. Infants will be checked for anaemia and iron deficiency at 6 months.

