**Approach and Methodology**

Design: We propose to conduct a cluster-randomised controlled trial of iron supplementation in pregnant women commenced before 16 weeks gestation. A placebo-controlled trial was not contemplated as we considered it unethical to withhold iron supplementation during pregnancy. The trial will have three intervention arms as follows: (1) one capsule of iron-folic acid (IFA) to be taken twice a week (60mg elemental iron /capsule, 2 capsules per week), or (2) one IFA tablet to be taken daily (60mg elemental iron /tablet; 7 tablets per week), or (3) one capsule of MMN to be taken twice a week (60 mg elemental iron/capsule, 2 capsules per week).

Supplements: We have chosen a local pharmaceutical manufacturer, Nam Ha Pharmaceutical Company, to produce the IFA and MMN supplements for the clinical trial. This company has produced IFA supplements for our Yen Bai WIFS program for the last 4 years and has WHO GMP certification. The supplements will require limited registration by the Ministry of Health for use for research purposes.

The formulation of the three types of supplements is shown in the table below.

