Lists kept at commune level will be used to identify all pregnant women in selected communes and all eligible women will be invited to participate by the research team, in conjunction with local village and commune health workers. In Hanam province we expect approximately 1990 live births per district/year (personal communication PI 4). All women in the trial communes that are <16 weeks gestation during the recruitment period will be considered for inclusion in the study. Women with complicated pregnancies (e.g. twins, diabetes, other medical conditions), or Hb<80 g/L will be excluded from the study and referred for medical treatment.

We expect recruitment to take approximately 8 weeks. However, a flexible approach will be taken and the research team will work closely with provincial counterparts to determine the best strategies for recruitment, which may involve recruiting over a longer time period. We plan to increase the recruitment of women in the first trimester of pregnancy by using village and commune health worker staff to inform women who are recently married or trying to become pregnant about the study, and to encourage them to come for early pregnancy testing. In this way we hope to recruit women from six weeks gestation. Written informed consent will be obtained at enrolment.

Reducing bias by blinding the researchers and participants to the intervention, and by training: The two arms of the trial with intermittent supplementation will be blinded. The supplements will be produced by Nam Ha Pharmaceutical Company, Vietnam, who will undertake the blinding process. The IFA and MMN capsules that will be taken twice a week will be identical and a code will be embossed on each blister pack, with the code known only to the manufacturer and the chairperson of the Data Monitoring and Safety Committee.

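### The haemoglobin and ferritin models name the baseline value as covariate but not the gestation at which it was sampled, which can run from about 6 to under 16 weeks

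*Protocol*

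**What the plan says.** **Model.** The Statistical Analysis section estimates "the difference in mean haemoglobin levels at 32 weeks, ferritin levels at 32 weeks" and other outcomes with a linear mixed model that has a random effect for commune. It then states: "For the outcomes haemoglobin and ferritin, the statistical analysis will adjust for the baseline measurement". Ferritin is log-transformed. The text under Aim 2 repeats the model and the baseline adjustment for the two twice-weekly arms. Neither place names gestation at sampling as a covariate, and neither says that the baseline value is the sole covariate.

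**Timing of the baseline sample.** Under maternal anaemia and micronutrient deficiencies, "venipuncture blood samples will be collected at enrolment, 32 weeks gestation and 6 months postpartum". The first sample thus follows entry and not a set gestation. On the lower end of entry, the recruitment text says: "In this way we hope to recruit women from six weeks gestation".

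**Upper limit of entry.** The design paragraph has "iron supplementation in pregnant women commenced before 16 weeks gestation". The recruitment text has "All women in the trial communes that are <16 weeks gestation during the recruitment period will be considered for inclusion in the study". The maternal schedule is headed "Enrolment <16 wks gestation", and the Research Plan and Figure 2 also use 16 weeks. The Lay Abstract differs: "All pregnant women who are <20 weeks gestation during the recruitment period will be invited to participate".

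**The concern.** If haemoglobin and ferritin change with gestation in early pregnancy, the same reading at 6 weeks and at 15 weeks does not describe the same iron status. The covariate then carries variation due only to when the woman enrolled, which weakens its link with the 32-week value. Because supplements start at enrolment and the outcome is fixed at 32 weeks, early entrants also have a longer exposure. The sample size section adds an interest in the mean change of ferritin to 32 weeks, and that change spans intervals of different length in different women.

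Two things would be at stake. The first is precision, which is affected even when arms are alike. The second is a shift in the estimate, which arises only if arms differ in mean entry gestation. The design leaves room for the second. Figure 2 places commune assignment before enrolment, local health staff encourage early pregnancy testing under a flexible recruitment approach, and the daily arm is open to participants and the field team.

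**Working it through.** **1. The plan's own figure.** Inputs from the sample size section: 408 women per arm, 12 per commune, 5% exclusions plus 15% loss, haemoglobin difference 6 g/L, SD 12 g/L, ICC 0.12. Two-sided 5% is assumed.
- n = 408 × 0.80 = 326.4 per arm
- Design effect = 1 + (12 − 1) × 0.12 = 2.32
- Effective n = 326.4 / 2.32 = 140.7
- z = 6 / (12 × √(2/140.7)) − 1.96 = 4.19 − 1.96 = 2.23, so power is 98.7% (stated: 98%)

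The figure reproduces. It uses the unadjusted SD, so it takes no credit for any covariate and nothing below changes it.

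**2. Interval from baseline to outcome.** 32 − 6 = 26 weeks at one end. 32 − 16 = 16 weeks at the other, so just over 16 for women enrolled before 16 weeks.

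**3. Assumptions that the protocol does not give.**
- Haemoglobin falls by b = 0.5, 1.0 or 1.5 g/L per week across the entry window.
- The correlation between baseline (at a given gestation) and 32-week haemoglobin is r = 0.3, 0.5 or 0.7.
- Entry is uniform over 6 to 16 weeks, so its SD is s = 10/√12 = 2.89 weeks and s² = 8.33.
- The SD is 12 g/L (variance 144) at both times, 32-week haemoglobin does not depend on entry gestation, and clustering is ignored in this step.

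**4. Formulas.**
- Baseline variance with timing spread: V = 144 + b²s²
- Residual variance, baseline alone: 144 − (144r)²/V
- Residual variance, baseline plus gestation: 144(1 − r²)
- Size of the shift per week of difference in mean entry gestation: b × 144r/V

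Low end (b = 0.5, r = 0.3): V = 146.08. The residual variances are 131.22 and 131.04, ratio 1.001. Shift = 0.5 × 43.2/146.08 = 0.15 g/L.

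High end (b = 1.5, r = 0.7): V = 162.75. The residual variances are 81.57 and 73.44, ratio 1.111. Shift = 1.5 × 100.8/162.75 = 0.93 g/L.

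| Fall (g/L per week) | r | Residual variance ratio | Shift (g/L per week of imbalance) |
|---|---|---|---|
| 0.5 | 0.3 | 1.001 | 0.15 |
| 0.5 | 0.5 | 1.005 | 0.25 |
| 0.5 | 0.7 | 1.014 | 0.35 |
| 1.0 | 0.3 | 1.005 | 0.28 |
| 1.0 | 0.5 | 1.018 | 0.47 |
| 1.0 | 0.7 | 1.053 | 0.66 |
| 1.5 | 0.3 | 1.011 | 0.40 |
| 1.5 | 0.5 | 1.038 | 0.66 |
| 1.5 | 0.7 | 1.111 | 0.93 |

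**5. Sensitivity to the entry pattern.** If women enter uniformly at 12 to 16 weeks, s = 4/√12 = 1.15 weeks and s² = 1.33. At the high end V = 144 + 2.25 × 1.33 = 147, the residual variance with baseline alone is 144 − 10160.64/147 = 74.88, and the ratio is 74.88/73.44 = 1.02. The largest loss falls from 11% to about 2%.

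**6. Direction.** An arm that enters earlier has a higher raw baseline, so the model expects a higher 32-week value from it and the adjusted estimate moves against that arm. Longer exposure, if it helps, moves the estimate the other way. The documents give nothing from which to net the two.

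No comparable figure can be given for ferritin, because the protocol offers no SD, correlation or trend for it.

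**The case against.** The strongest reply is that the stated analysis is not wrong. A baseline-adjusted mixed model with a commune effect is a valid analysis of a cluster-randomised comparison, whenever the baseline was drawn. A reader might infer that the protocol adjusts for baseline and nothing else. It does not say so, and a fuller covariate list may sit in an analysis plan that is not among the documents. That objection stands, which is why the point is an improvement to a valid model and not an error in it.

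A reader might also infer a biased treatment effect. The documents do not show one. Each arm has 34 randomised communes, the recruitment approach is described once for the whole trial, and the two twice-weekly arms are blinded with identical capsules, so Aim 2 has no evident route to unequal entry. That early-testing promotion follows allocation is itself an inference from Figure 2. Imbalance is possible, chiefly against the open daily arm, but it is not established.

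The size is assumption-bound as well. Six weeks is a hope and not a lower limit. The planning SD comes from women at 12 to 22 weeks, so it already contains some gestational spread.

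Finally, a reader might stretch the exposure range by using the 20-week limit. That limit appears as an entry criterion only in the Lay Abstract, against five places that give 16, so it does not support a wider range here. What remains is that the protocol describes this model twice and leaves out a variable that it must collect anyway.

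**Conclusion.** The point holds as a minor, nearly free improvement. The model as written is valid. With balanced entry the cost of leaving out gestation at sampling is a residual variance about 0.1% to 11% higher for haemoglobin, and about 2% at most if women enter uniformly at 12 to 16 weeks. If arms differ in mean entry gestation, each week shifts the haemoglobin estimate by about 0.15 to 0.93 g/L, or 2.5% to 15.5% of the 6 g/L target, apart from any opposite effect of longer exposure. All these sizes rest on the assumed weekly fall, correlation and entry pattern. A reader might take the point as a threat to the trial's main conclusion. It is not: the primary outcome is birth weight, which this adjustment does not touch, and the 98% haemoglobin power stands.

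The conflict between the 16- and 20-week entry limits is real whatever the model, but it is close to clerical.

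**What to change.** - In the Statistical Analysis section and in the matching text under Aim 2, add gestational age at the enrolment sample as a prespecified continuous covariate beside the baseline value, in the maternal haemoglobin and log-ferritin models. Since the outcome is fixed at 32 weeks, this one term also carries the interval from baseline to outcome.
- Report entry gestation by arm, so that any imbalance can be seen.
- Separately, reconcile the entry limit in the Lay Abstract with the one in the Research Plan, design paragraph, recruitment text, Figure 2 and maternal schedule.

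The cost is one sentence in each model statement, one degree of freedom and one row in a baseline table. No new data are needed, because gestation must already be known to judge eligibility and to time the 32-week visit. Fixing the covariate in advance also avoids a choice made after an imbalance has been seen.

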
Research Plan

We will conduct a cluster-randomized controlled trial in Hanam province, where there were 11,551 recorded births in 2008. We will randomize 102 communes to one of the three intervention arms of the study, and all women that are pregnant during the recruitment period and less than 16 weeks gestation will be invited to participate. We will recruit 1224 pregnant women who will take either (i) two capsules of iron-folic acid per week (60 mg elemental iron/capsule), or (ii) one capsule of iron-folic acid per day (60mg iron/capsule), or (iii) two capsules of MMN per week (60mg iron/capsule).

Aims 1. To compare the effect of twice weekly provision of iron-folic acid or MMN supplements, with the recommended daily iron-folic acid supplements during pregnancy on maternal and infant outcomes (including the primary outcome of birth weight; and secondary outcomes of maternal haemoglobin and ferritin at 32 weeks, and infant height for age z scores, haemoglobin, ferritin and cognitive developmental scores at 6 months of age).

2. To compare the effect of twice-weekly provision of iron-folic acid supplements with twice weekly MMN during pregnancy on maternal and infant outcomes, using similar outcomes to Aim 1.

Outcomes and Significance: Vietnam is currently considering a nationwide weekly iron-folic acid or MMN supplementation program for non-pregnant women of reproductive age. Evidence from this study will clarify whether this approach is also suitable for use when women become pregnant. This would increase availability of supplements by allowing easier distribution at village level, and would likely reduce side effects compared to the currently recommended (although poorly administered) daily provision of iron-folic acid supplementation. It will extend previous studies by measuring clinical outcomes of different iron supplementation approaches and the impact on infant outcomes.

| Principal Investigator Associate [name] |
| --- |
|  |
|  |
| Specific Aim(s) of the Project |

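### The stated birth-weight model names no covariates, so it makes no use of maternal size at enrolment, which is scheduled for every woman; prespecifying it would modestly sharpen the primary comparison

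*Protocol*

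**What the plan says.** The aims name birth weight as the main endpoint ("including the primary outcome of birth weight"). The Statistical Analysis section gives one model for haemoglobin, ferritin, birth weight and height-for-age: a linear mixed model with a random effect for commune. It then adds a covariate for two of the four: "For the outcomes haemoglobin and ferritin, the statistical analysis will adjust for the baseline measurement". The text under Aim 2 repeats both statements for the comparison of the two twice-weekly arms. Neither place names a covariate for birth weight or height-for-age.

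On data, the section on maternal and infant anthropometry says: "Maternal anthropometry will be assessed by mid-upper arm circumference, body weight and height in all participants at enrolment". Figure 2 and the schedule of maternal assessments agree. Gestation at enrolment must also be established, because entry is limited by gestational age.

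The Sample size calculations section plans "34 communes / 408 pregnant women per treatment arm" and gives the birth-weight case as "100g for birthweight (power = 81%, SD= 389g, ICC=0.03".

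**The concern.** Of the three outcomes that were sized, the primary one has the least power: 81%, against 98% for haemoglobin and 93% for height-for-age. Yet covariate adjustment is named only for haemoglobin and ferritin. Maternal size at enrolment is measured before supplements start and can be expected to relate to infant size, so it is a natural covariate for birth weight.

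Two things are at stake. One is precision: variance explained by a baseline covariate drops out of the standard error of the arm difference. The other is chance imbalance. Only 34 communes go to each arm, and the section on treatment allocation names no stratification factor, so the arms could differ somewhat in average maternal size. Adjustment accounts for such imbalance in the covariates that are included, though not in others.

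**Working it through.** **Inputs from the Sample size calculations section**
- Difference 100 g, SD 389 g, ICC 0.03, stated power 81%.
- 408 women in 34 communes per arm, so a mean cluster size of 12.
- Losses: "it is expected that 5% of women will be excluded due to pregnancy complications and 15% will be lost to follow-up".
- The confidence level is 95%, read here as two-sided alpha 0.05.

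**Step 1: reproduce the stated power**
- Women analysed per arm: 408 × (1 − 0.05 − 0.15) = 326.4
- Design effect: 1 + (12 − 1) × 0.03 = 1.33
- Effective size per arm: 326.4 / 1.33 = 245.4
- SE of the difference: 389 × √(2 / 245.4) = 35.12 g
- Power: Φ(100 / 35.12 − 1.96) = 81.3%, against 81% stated

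The same steps give 98.7% for haemoglobin (stated 98%) and 92.8% for height-for-age (stated 93%). The birth-weight figure therefore rests on the full SD, with no allowance for covariates. Applying the two losses multiplicatively gives 81.6%. Taking the design effect at the reduced cluster size of 9.6 gives about 83%.

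**Step 2: add prognostic covariates**

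The protocol gives no R² of birth weight on maternal size, so a range is assumed. With the ICC held at 0.03, SE(adjusted) = 35.12 × √(1 − R²), the CI half-width is 1.96 × SE, and the difference detectable at 80% power is (1.96 + 0.84) × SE.

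| Assumed R² | Power for 100 g | 95% CI half-width | Detectable at 80% power |
| --- | --- | --- | --- |
| 0 | 81.3% | 68.8 g | 98.4 g |
| 0.02 | 82.0% | 68.1 g | 97.4 g |
| 0.05 | 83.2% | 67.1 g | 95.9 g |
| 0.10 | 85.1% | 65.3 g | 93.3 g |
| 0.15 | 87.1% | 63.5 g | 90.7 g |

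**Step 3: test the constant-ICC assumption**

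Step 2 supposes that the covariates shrink within-commune and between-commune variance in proportion. Suppose instead that an R² of 0.10 comes wholly from within communes.
- Total variance: 389² = 151,321. Between communes: 0.03 × 151,321 = 4,540.
- Residual total: 0.90 × 151,321 = 136,189. New ICC: 4,540 / 136,189 = 0.033.
- Design effect: 1 + 11 × 0.0333 = 1.367. Effective size: 326.4 / 1.367 = 238.8.
- SE: √(136,189 × 2 / 238.8) = 33.8 g. Power is about 84%, against 85% in the table.

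The gain is slightly smaller, in the same direction.

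**The case against.** The strongest reply is that the sentence on baseline adjustment concerns an outcome's own earlier value. Birth weight and infant height-for-age have none, so they could not appear in it, and their absence is no decision against maternal covariates. That stands. A reader might infer that the protocol has ruled out adjustment, but it nowhere does so. It names a model for birth weight and puts no covariate in it.

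A second reply is that covariates are commonly settled in the statistical analysis plan, which is not shown here and may already list them. That is possible. The point is kept because the protocol itself states the model for the primary outcome and sets covariates for two secondary outcomes in two places; if the analysis plan covers birth weight, a cross-reference is enough.

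Third, a mixed model without covariates is valid and meets the stated power target. That also stands.

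A reader might also go further and call the primary outcome underpowered. The confidence intervals in the preliminary birth-weight table imply SDs of about 364 g and 447 g, pooled about 419 g, at which power would be about 75%. The documents do not establish this. The intervals may already allow for clustering, which would inflate the implied SD, and the 389 g is attributed to unpublished data that cannot be seen. It is a separate question, and this point does not rest on it.

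Nor do the documents support treating infant sex as available, since no list of birth measurements mentions it.

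**Conclusion.** The point holds as a worthwhile improvement. The protocol contains no error or contradiction here, and its 81% power reproduces without adjustment.

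For an assumed R² of 2% to 15%, power for 100 g rises by about 1 to 6 percentage points, to between 82% and 87%. The CI half-width shrinks from about 69 g to between 68 g and 64 g. The size rests entirely on that assumed R² and on a roughly constant ICC. The direction is secure only if the covariates do predict birth weight. In a linear model the adjusted and unadjusted analyses estimate the same difference in means, so the 100 g target keeps its meaning.

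It would go too far to say that precision is lost at no cost or that adjustment removes imbalance. The gain is modest, it needs some extra work, and only the included covariates are balanced.

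**What to change.** In the Statistical Analysis section and under Aim 2, add a sentence for birth weight and height-for-age that prespecifies these fixed covariates: maternal height and weight (or BMI) at enrolment, and gestational age at enrolment. The last also puts weights taken at different weeks of pregnancy on a common footing. Keep the random commune effect. Report the estimate without covariates as supportive. Include infant sex only if it is confirmed to be recorded at birth. Fix the list before outcome data are seen, and say how missing covariate values will be handled so that no woman drops out of the primary analysis for lack of one.

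The cost is a sentence or two in the protocol (or a cross-reference, if the analysis plan already covers this), a little more analysis work, and the handling of any missing covariate values. No new visit, measurement or participant is needed.
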